**Study B:**

Saliva samples will be collected during the first week postpartum, at 1, 3, 6 and 12 months postpartum. Whenever children are already spilling saliva, this can be collected directly with a saliva swab (i.e. a soft inert polymer swab that will take up the saliva). When children are not spilling saliva, the saliva swab can also be introduced gently into the mouth in a similar way as a pacifier. The child has to suck or chew on the saliva swab for several seconds before the swab will be retrieved. The saliva swab will afterwards be stored in a collection tube on ice for transportation to the lab. At the lab, saliva will be removed for the swab by using a centrifuge. The collected saliva will be aliquoted in several tubes, maximal 900uL per tube. In case of lower amounts of saliva yields, tubes will contain less the 900uL, this will be logged for future sample usage.

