**Study B:**

In the sub study we will also collect additional samples to research what the influence of breastfeeding is on immune development, compared to other routes that are enrolled in the transfer of maternal immunity to the neonate. This will be done in a subgroup of 20 mother-child dyads. The samples that we will collect are cord blood samples, a maternal blood sample and an amniotic fluid sample. Jacobino et al. showed that antibodies retrieved form human amniotic fluid protected mice pups against RSV-infections (Jacobino2016). Very little is known about the protective value antibody titters in cord blood. Active placental transport of maternal antibodies to the neonatal blood has been described, but little is known about the effectiveness of these antibodies (Kohler1966). To obtain more insight in the effect of the antibodies that are being transferred by breastfeeding, we will compare the effect of breastfeeding to the antibodies in cord blood and amniotic fluid. To evaluate the effect of the maternal Bordetella pertussis vaccination on (pertussis-specific) immune development in children, we will also collect saliva samples at 1 week, 1 month, 3 months, 6 months and 12 months postpartum. Saliva samples offer an ideal method to evaluate the (Bordetella-pertussis specific) immune development during the first year of life since saliva antibody titters correlate well with serum titters but saliva samples are considered to be non-invasive.

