**Study B:**

Secondary objective 5:

To describe antibody concentrations in compartments relevant to materno-fetal antibody transfer. We will define the association between maternal serum, breast milk antibodies, cord blood, amniotic and infant antibodies over time. This study is performed while maternal pertussis vaccination is introduced. We will therefore analyse total and pertussis-specific antibody concentrations.

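### Study B lets an infant's drooling decide how saliva is collected and does not record the route, so a change in salivary antibody with age could partly reflect collection and could not be checked

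*Protocol*

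**What the plan says.** Protocol 5.2 (Saliva sampling, Study B) sets the schedule: "Saliva samples will be collected during the first week postpartum, at 1, 3, 6 and 12 months postpartum". Two routes are then allowed. The first is for drooling infants: "Whenever children are already spilling saliva, this can be collected directly with a saliva swab". The second is for the others: "When children are not spilling saliva, the saliva swab can also be introduced gently into the mouth in a similar way as a pacifier". For that second route, "The child has to suck or chew on the saliva swab for several seconds before the swab will be retrieved". After collection both routes are handled alike: ice, centrifuge, aliquots.

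The only departure that 5.2 asks staff to log is a low yield: "In case of lower amounts of saliva yields, tubes will contain less the 900uL, this will be logged for future sample usage". The infant saliva code in 9.1 holds the study ID, participant number, sample type, moment of sampling and tube number. It has no element for route.

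The repeated samples serve secondary objective 5 in section 2: "We will define the association between maternal serum, breast milk antibodies, cord blood, amniotic and infant antibodies over time". That objective adds: "We will therefore analyse total and pertussis-specific antibody concentrations". The introduction (section 1, Study B) gives the aim of the series as evaluating infant immune development after maternal pertussis vaccination.

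**The concern.** One route takes up saliva that has already left the mouth. The other takes saliva produced while the infant sucks or chews. The choice between them is not fixed by design and not left to chance: it follows whether the infant is drooling at that visit. The word 'already' in the instruction hints that drooling is something infants grow into, although the protocol does not say so. If it is, the mix of routes shifts across the five visits in the same infants.

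The planned quantity is a concentration, so it depends on how dilute the saliva is. Should the two routes differ in dilution, a drift in route over age would appear as a drift in antibody. It could then be read as waning maternal antibody or as the infant's own response. Saliva is the only infant sample that Study B takes repeatedly, so no infant serum series exists against which to check the course. Because the route is not recorded, the analyst could neither stratify by it nor set aside samples taken the other way.

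**Working it through.** **The plan's own figures.** The protocol gives no figure on this point. The only Study B calculation is the sample size in 4.4, and it reproduces. With 9 per group, a difference of 88.3 and SDs of 80.0 and 18.0, the standard error is √(80²/9 + 18²/9) = √747.1 = 27.3. The noncentrality is 88.3/27.3 = 3.23. A two-sided unequal-variance t-test with 8.81 degrees of freedom then has power 81.7%, against the stated 82%. That calculation is not in dispute and does not bear on collection route.

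**Inputs from the protocol.** Five visits from week 1 to month 12 (5.2); two routes chosen by drooling state (5.2); no record of route (5.2, 9.1); 20 dyads (section 1, Study B).

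**Inputs the protocol does not give.** These are assumptions:
- p, the share of infants sampled by the drooling route at a visit;
- r, the ratio of antibody concentration between the drooling route and the in-mouth route.

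**Formula.** Suppose there is no true change with age and r is constant. A visit's mean log concentration is shifted by p × ln r, so the apparent geometric-mean ratio between two visits is

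r^(p_late − p_early).

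**Results, with drooling at 0% at the earlier visit:**

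| r | later share 50% | later share 80% |
|---|---|---|
| 1.00 | 1.00 | 1.00 |
| 1.25 | 1.25^0.5 = 1.12 | 1.25^0.8 = 1.20 |
| 1.5 | 1.5^0.5 = 1.22 | 1.5^0.8 = 1.38 |
| 2.0 | 2.0^0.5 = 1.41 | 2.0^0.8 = 1.74 |

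The direction is not known either. With r below 1 and drooling rising from 0% to 50%, the apparent ratio is 0.95 for r = 0.9, 0.87 for r = 0.75 and 0.71 for r = 0.5. If the drooling share is equal at both visits, for example 20% and 20%, the exponent is zero and the ratio is 1.00 whatever r is.

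**Illustration of how visible this could be.** Assume 20 infants, a log-scale SD of 0.8, a within-infant correlation of 0.5 and a paired t-test of week 1 against 6 months. In simulation, r = 1.25 / 1.5 / 2.0 then gave a falsely significant change in about 16% / 38% / 79% of studies with an 80% later share. With a 50% later share the figures were about 9% / 19% / 39%, and with r = 1 about 5%. The SD, the correlation and the test itself are assumptions. The protocol plans no such test, so these rates only give a sense of scale.

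**The case against.** The strongest reply is that the causal chain is not in the protocol. It does not say how drooling changes with age, and it does not say that the two routes give different concentrations. That stands: if either condition fails, there is no distortion. A reader might infer that the Study B time course is biased by a known amount, or that the routes amount to two different devices. The document supports neither reading. Both routes use a saliva swab and the same processing, and the instruction is permissive, so staff might use the mouth throughout. Nothing in the protocol ensures that they do, however.

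A reader might also take the false-significance rates as error rates of the planned analysis. They are not. Objective 5 describes concentrations and associations between compartments. For associations between infants at a single visit, mixed routes would mainly add noise rather than an age artefact.

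Scale and timing matter too. The one contrast for which Study B is sized is 100.7 against 12.4, about 8-fold (100.7/12.4 = 8.1), far larger than the shifts shown above. The 12-month sample is the only one for which section 3 gives a scientific reason, and no drooling share is known for it; the week 1 to 6 months illustration does not cover it.

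What survives is narrow. A written rule ties collection to an infant state that can shift with age, and it leaves no trace in the data. A later analysis plan cannot recover a route that nobody wrote down.

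**Conclusion.** The point holds as potential, uncheckable confounding of age with collection route. It does not hold as an established bias. Under the assumed range (route ratio 1.25 to 2.0, drooling rising from 0% to 50–80%), an apparent change of about 1.1- to 1.75-fold could arise with no true change. With equal concentrations by both routes, or a constant drooling share, it is exactly 1.00. It touches a secondary, descriptive objective in 20 dyads and leaves the primary endpoint alone. It is a minor to moderate point, worth making because the improvement is cheap and has to be made before the samples are taken.

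**What to change.** In 5.2, Saliva sampling, Study B:
- Make the in-mouth swab with a defined collection time the default at all five visits for every infant, drooling or not. Study C already uses an in-mouth collector with a defined end point (pad saturated, 60–90 seconds), although with a different device and only at 3 months.
- Record the route for each sample, as one field in the sample log.
- In a sensitivity analysis of the time course, adjust for route or leave out samples taken by the other route.

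A common collection time does not fully equalise sucking between a newborn and a one-year-old, so some link between age and saliva flow may remain. The ratio of pertussis-specific to total antibody in the same sample can be added as a supplementary analysis, because both are already planned and a common dilution factor cancels. It cannot replace the concentrations: it is a different quantity, it cannot correct total antibody, and total antibody may itself change with age.

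The cost is a wording change and one extra log field, with no new visits, swabs or assays. The small downside is that direct collection is no longer the default for drooling infants.

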**Study C:**

Saliva will be collected by a parent in the week before the 3 month sample collection. Saliva will be sampled with Micro•SAL™ for Children according to manufacturer’s protocol. The pad of the Collector will be placed in the mouth of the infant until the pad is saturated (60-90 sec.). The saturated collector will be pushed into the compression tube, which is firmly connected with its base into an Eppendorf tube. The Eppendorf tube with saliva sample will be stored at -20°C in the freezer at the participant’s home, until collection by the researcher.

*Questionnaires:*

**Study A:**

Data will be collected using questionnaires and by interviewing general practioners and/or pharmacists.

Questionnaires will be send to parents using Castor EDC. Parents will receive a baseline questionnaire at moment of entering the study, which will cost them about 20-30 minutes to fill in. Consecutively they will receive every 2 weeks a short questionnaire to monitor infectious episodes, feeding habits, gut discomfort and crying of the infant and to screen for any infectious episodes in mothers, which takes 1-2 minutes each to fill in. The 2 weekly questionnaire will be expended to a longer list at 6 months and 12 months postpartum to screen children for allergies developed during the first year. Parents will receive questionnaires through email.

**Study C:**

The questionnaires for the dietary assessment will be send via e-mail. Parents receive login information for the tool which is reached via a website page. The FFQ will be send at 2 month and 4 month postpartum and will take 45-60 min. to fill in each. The 24h recall will be send at 1 month and 3 month postpartum and will take 20-30 min. fill in each.

## Withdrawal of individual subjects

Subjects can leave the study at any time for any reason if they wish to do so without any consequences. The investigator can decide to withdraw a subject from the study for urgent medical reasons.

### Specific criteria for withdrawal (if applicable)

Only when not one breast milk sample is collected that is stored on the proper conditions (i.e. stored in the fridge or on ice after collection), participants can be withdrawn from the study

## Replacement of individual subjects after withdrawal

A new mother-child dyad will be recruited to replace a withdrawn dyads when withdraw occurs before the first sample is taken.

## Follow-up of subjects withdrawn from treatment

na.

## Premature termination of the study

na.

# SAFETY REPORTING

na

# STATISTICAL ANALYSIS

The section on statistical analysis only describes how the quantitative analyses will be done, answering the primary and secondary research objectives.

## Primary study parameter(s)

## The association between 2’FL concentrations and the number of medically attended respiratory tract infections during the first year of life will be determined using Poisson regression analysis, adjusted for potential confounders. Potential confounders will be identified by a literature search, complemented by expert knowledge. One such potential confounder is like 3’SL that is both suggested to exert a direct antiviral effect as well as to be associated with a shorter lactation duration (Azad201,; Laucirica2017, Pandey2018).

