**Study A:**

**Study design:** Observational birth cohort study

**Study population:** healthy mother-child dyads recruited during the first month postpartum.

**Intervention (if applicable)**: none.

**Main study parameters/endpoints:** The main study parameter is the number of MARI’s (Medically Attended Respiratory tract Infections) during the first year of life. This will be measured using questionnaires that parents have to fill in every two weeks. In the same questionnaire, the gut discomfort and crying time of the infant is assessed for the first six months.During the 6-month and 12-month questionnaire, questions about allergy development are added to the questionnaire.

In addition to the questionnaire, we will also collect samples both from the mother as from the child.

Human milk samples will be collected from the mothers during the first week postpartum and at 1, 3 and 6 months postpartum. In human milk, we will measure the antibody titters (both isotype as well as pathogen specific), oligosaccharide composition and immune cell repertoire. A subgroup will be used to analyse extra cellular vesicles (n=15). Since the extracellular vesicle analyses requires bigger sample volumes (at least 5mL sample is required for vesicle analyses, preferably more), only mothers that donate a large amount of human milk at the first week postpartum will be analysed for extracellular vesicles.

Amniotic fluid and cord blood and maternal blood samples will be collected in a subgroup of 20 mother-child pairs. Cord blood and amniotic fluid will be collected within the first hours postpartum from the umbilicus. Maternal blood samples will be collected during the first week postpartum. Blood and amniotic fluid samples will be analysed on antibody, oligosaccharide and extracellular vesicle composition and immune cell repertoire

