## Sample size calculation

## Study A:

A sample size of 1000 participants participants has an 80% power to detect a ratio of the means of 0.91 in those with vs. those without a medically attended LRTI using a two-sided two-sample t-test, assuming that 10% of the cohort participants have a medically attended LRTI (N=100) and that the 2’FL HMO concentration in the population has a mean of 3g/L, a standard deviation of 1g/L, and a normal distribution (Donovan2016). The significance level (alpha) is 0.05. The sample size was calculated using Power Analysis for Sample Size (PASS) 2008.

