## Secondary study parameter(s)

## The association between 2’FL concentrations and the number of allergies and total number of infections during first year of life will be analysed in a similar fashion as for the primary outcomes.

The 24h recalls filled in by the mother, will be checked on missing data in the same week by trained staff When missing data is expected, for example 1 slice of bread but 5 portions of bread toppings are noted, the researcher or research nurse will contact the participant. Notes from the participants will also be processed by the trained staff.

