# ADMINISTRATIVE ASPECTS, MONITORING AND PUBLICATION

## Handling and storage of data and documents

Data, samples and documents will be stored using a specific code. This code for samples consists of: study ID (i.e. UMCUPRIMA) an anonymised participant number (e.g. for participant 1 this will be 10001), moment of sampling (e.g. week 1 is W1) and sample number including type of sample (W for water fraction, F for fat and C for cellular fraction). Combining this codes will result in the following; for example participant 1 donated milk during the first 1 week postpartum and we will label a tube with the first part of the water fraction, the code will be: UMCUPRIMA.10001.W1.W01.

The coding system for neonatal blood samples from the placenta will be composed as follows: it consists of study ID (i.e. UMCUPRIMA) an anonymised participant number (e.g. for participant 1 this will be 10001) (this number will be similar to the milk sample number), indication it is neonatal blood (BLOOD.NEO)In case a mother gives labour to a twin, the N will be followed by either a 1 or 2. The 1 and 2 should correspond to the castor ID’s that will be used for sending the questionnaires.

The coding system for maternal blood samples will be composed as follows: it consists of study ID (i.e. UMCUPRIMA) an anonymised participant number (e.g. for participant 1 this will be 10001)(this number will be similar to the milk sample number), indication it is maternal blood (BLOOD.MAT).

The coding system for amniotic fluid samples will be composed as follows: it consists of study ID (i.e. UMCUPRIMA) an anonymised participant number (e.g. for participant 1 this will be 10001)(this number will be similar to the milk sample number), indication it is maternal blood (AMNIOTICF.).

The coding system for infant saliva samples will be composed as follows: it consists of study ID (i.e. UMCUPRIMA) an anonymised participant number (e.g. for participant 1 this will be 10001), indication infant saliva sample (SALIV.INF.), moment of sampling (e.g. week 1 is W1) and number of tube (e.g. the first tube is T1). Combining this codes will result in the following: for example the first tube of saliva sample of participant 1 that donated saliva during the first 1 week postpartum, the code will be: UMCUPRIMA.10001.SALIV.INF.W1.T1.

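### Section 7.1 names Poisson regression for a recurrent infection count with no allowance for overdispersion; with model-based standard errors the 2'FL confidence interval is likely to be too narrow

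*Protocol*

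**What the plan says.** The Summary (Study A) defines the outcome as a count: "The main study parameter is the number of MARI’s (Medically Attended Respiratory tract Infections) during the first year of life". Section 7.1 fixes the model: the association with 2'FL "during the first year of life will be determined using Poisson regression analysis, adjusted for potential confounders". The confounders are to come from literature and expert knowledge, and only 3'SL is named.

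Section 7.2 carries the approach to two further outcomes: "number of allergies and total number of infections during first year of life will be analysed in a similar fashion as for the primary outcomes".

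Section 9.1 shows that twins can be enrolled: "In case a mother gives labour to a twin, the N will be followed by either a 1 or 2". The next sentence there links that digit to separate questionnaire IDs, so each twin contributes a count while both share one mother's milk.

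Nowhere does the protocol mention overdispersion, robust or scaled standard errors, a negative binomial model, or the handling of siblings. Nor does it say that model-based standard errors will be used.

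**The concern.** Model-based Poisson inference sets the variance of the count equal to its mean, given the covariates. The protocol itself points to reasons why infants differ in their underlying rate:

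- other children in the household, parental smoking and parental chronic disease (5.1.3);
- season (7.1);
- gestational age, since only births before 32 weeks are excluded (4.3);
- uneven case finding, since counts may come from questionnaires, general practice records or imputation (7.4).

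Whatever part of this the covariates do not absorb makes the variance exceed the mean, and the model-based standard error is then too small. The 5% level of the primary 2'FL test, and the coverage of its interval, are at stake.

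**Working it through.** **The plan's own figure.** Section 4.4 gives no power, mean or variance for the Poisson model. Its only power statement is "80% power to detect a ratio of the means of 0.91", for a two-sided t-test of 2'FL in 100 infants with and 900 without a medically attended lower respiratory infection (SD 1 g/L). A difference of 0.09 × 3 = 0.27 g/L gives 72.5%. Group means of 3 and 3/0.91 give 80.3%, and a log-ratio test with coefficient of variation 1/3 gives 78.6%. The stated 80% is therefore reachable under common readings. It has no bearing on the Poisson variance.

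**Inputs.** From section 4.4: N = 1000, two-sided alpha 0.05, and 10% of infants with a medically attended lower respiratory infection. Assumed, because the protocol gives none of them: the mean MARI count μ, the heterogeneity k, the share of twins, and the correlation within twin pairs.

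**Step 1: effect of a given dispersion.** Let φ be the variance/mean ratio left after covariates. Then type I error = 2·(1 − Φ(1.96/√φ)), and the model-based interval has 1/√φ of its correct width.

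| φ | Type I error | Width relative to correct |
|---|---|---|
| 1.0 | 5.0% | 1.00 |
| 1.1 | 6.2% | 0.95 |
| 1.25 | 8.0% | 0.89 |
| 1.5 | 11.0% | 0.82 |
| 2.0 | 16.6% | 0.71 |
| 2.5 | 21.5% | 0.63 |

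**Step 2: φ at the protocol's only event rate.** For negative binomial counts φ = 1 + kμ. If 10% of infants have at least one event, (1 + kμ)^(−1/k) = 0.9, so μ = (0.9^(−k) − 1)/k.

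| k (assumed) | μ | φ | Type I error |
|---|---|---|---|
| 0.25 | 0.107 | 1.03 | 5.3% |
| 0.5 | 0.108 | 1.05 | 5.6% |
| 1 | 0.111 | 1.11 | 6.3% |
| 2 | 0.117 | 1.24 | 7.8% |

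**Step 3: φ for the actual endpoint.** The 10% is for lower respiratory infections, whereas the endpoint covers all medically attended respiratory infections and must be at least as frequent. The table uses assumed means and k. The simulations had N = 1000, no true 2'FL effect, no covariates and 3000 runs per cell (simulation error about 0.4 points at a 5% level).

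| μ | k | φ | Formula | Simulated, model-based | Simulated, robust |
|---|---|---|---|---|---|
| 0.5 | 0.5 | 1.25 | 8.0% | 8.1% | 5.2% |
| 0.5 | 1 | 1.5 | 11.0% | 9.9% | 5.1% |
| 1 | 0.5 | 1.5 | 11.0% | 11.0% | 5.2% |
| 1 | 1 | 2.0 | 16.6% | 16.3% | 5.2% |
| 1.5 | 0.5 | 1.75 | 13.8% | 12.9% | 5.4% |
| 1.5 | 1 | 2.5 | 21.5% | 21.8% | 5.6% |

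Without overdispersion the model-based test gave 4.4% to 5.7%. Across all simulated scenarios, robust or Pearson-scaled standard errors gave 4.4% to 5.9%.

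**Step 4: twins alone.** Design effect = 1 + (share of twin infants) × (within-pair correlation). With an assumed 2% to 6% of infants and a correlation of 0.2 to 0.5, it is 1.004 to 1.03, and the type I error is 5.05% to 5.35%.

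**The case against.** The strongest reply is that section 7.1 contains no false statement. It names a model family and is silent on the variance estimator. Poisson regression with robust standard errors fits its wording, and such details are often left to a statistical analysis plan, which may exist but was not available here. This stands as a limit on severity, and a plan that specifies robust errors would settle the point. It does not remove the point: the protocol commits the primary test to a named model whose default variance suits this outcome poorly, and a better choice costs almost nothing.

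Second, what counts is the dispersion after adjustment. The protocol collects household composition, birth characteristics, smoking and education, and it considers season. These may absorb part of the heterogeneity, by an amount that cannot be derived from the documents. The percentages above are therefore before any such reduction.

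Third, the simulations show only what follows from an assumed φ; they are not evidence that φ is large in this cohort. That is also right.

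From the allergy outcome a reader might infer that it is close to yes/no, so that Poisson errors are too wide, or that an allergy reported at both 6 and 12 months is counted twice. The protocol supports neither. It speaks of a number of allergies, gives no prevalence, and nowhere says that positive answers are added up.

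**Conclusion.** The point holds in conditional form. Section 7.1 applies Poisson regression to a recurrent count that is likely to be overdispersed and makes no allowance for it. With model-based standard errors, the 2'FL interval is then likely to be too narrow.

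The type I error is about 5% to 8% at the protocol's 10% rate for lower respiratory infections (assumed k 0.25 to 2). It is about 8% to 22% for an assumed MARI mean of 0.5 to 1.5 with k 0.5 to 1. Both ranges assume negative binomial counts, heterogeneity unrelated to 2'FL, and no help from covariates.

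A reader might infer that the error will be well above 5%, or that a false protective claim is several times as likely as stated. The documents do not support this, because they give neither the mean nor the variance of the count, and the low end of the range is close to 5%. Dependence between infants is a minor part: twins are the only clustering the protocol shows, and on their own they add at most about 0.4 points. The rating is should-fix, not must-fix.

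**What to change.** In section 7.1, state: *Poisson regression with robust (sandwich) standard errors clustered on mother*. This keeps the named model and also covers twin pairs. Negative binomial regression is the alternative; one of the two should be chosen before the data are seen.

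In section 7.2, apply the same rule to the total number of infections and the number of allergies. Robust errors also correct any underdispersion in the allergy count, so that endpoint need not change.

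The cost is a line of wording in each section and a software option, with no new data. Intervals for the infection counts become somewhat wider, by a factor of √φ: about 1.12 at φ = 1.25 and 1.41 at φ = 2.
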